## Methods and analysis

### Design

An intervention development and feasibility study including focus group discussions, a historically controlled evaluation and process evaluation.^29 30^ The intervention is implemented in two antenatal care clinics in mid-Sweden. The feasibility and piloting includes testing procedures for acceptability, estimating the likely rates of recruitment and retention of women and the calculation of appropriate sample sizes for future controlled trials. Complex interventions that are adjusted to local, specific^31^ or personal needs^32^ are likely to be more effective than completely standardised models.^29^ Key principles underpinning the study are therefore:

Active involvement of Somali parents and midwives in needs assessment and care design.Attention to language and contextual factors.Flexibility in study methods to respond to issues as they arise.A care model ready to continue or be replicated after the project concludes with only minor adjustments.

Hooyo consists of four phases with process evaluation activities informing study progress. Phase I is the preparation phase, including needs assessment, the development of contextual understanding and building a logic model for the project. Phase II includes the development of the intervention and of the evaluation tools, and phase III involves implementation and evaluation of the intervention using historical controls. In phase IV, the implementation process, the feasibility and the mechanisms of impact are evaluated, including contextual factors, using Moore’s Process Evaluation of Complex Interventions as an overarching framework.^30^ Phases I and II were conducted in 2016–2017. Recruitment and data collection for the historically controlled evaluation (phase III) and process evaluation (phase IV) commenced in late 2016 and will be completed during 2020. Women in the control group were recruited between October 2016 and April 2018 and recruitment of women into the intervention began in May 2018 and will be complete in December 2019. Final data collection will be completed by July 2020. The paper covers methodological aspects of all four phases of the study.

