#### The intervention: gANC

The intervention consists of gANC offered at both sites, modified to the needs in each site and group. Women are allocated to a group with women at similar stages of pregnancy within a 4-week gestational age span. From the second visit (gestational weeks 20–26), they receive gANC. Each group will consist of six to eight women and partners (or another support person) for optimal group dynamics and dialogue. While reports of gANC internationally involve numbers in groups of 5–20 in low-income to middle-income countries^41^ and 8–12 in high-income countries,^42^ the need to provide interpreting during groups sessions led to the choice of a somewhat smaller group size as being appropriate to allow all group members a chance to participate in the discussions. Partners are generally encouraged to participate in Swedish ANC, and hence this will be the point of departure also for the gANC but with the final decision about partner participation taken by the women included in each group. Frequency and number of sessions follow the national Swedish programme for antenatal care, that is, eight to nine appointments during a normal pregnancy. Each visit includes a group session for 1 hour, facilitated by one of two midwives assigned to the group and with interpreter assistance. Although each group session has a focus on a theme related to pregnancy, birth or parenting in line with national recommendations,^17^ particular emphasis will be given to issues and questions raised by the participants. Group care allows women to talk with each other and share their experiences in their own language. They also hear midwives’ responses to other women’s questions, expanding the dialogue and information sharing that can occur between midwives and women. The presence of an interpreter facilitates communication between the women and the midwives.

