#### Sample size issues

Our main purpose is to develop and test the feasibility of the intervention and study processes and in so doing, also provide information to inform sample size calculations for possible future randomised controlled trials. Nevertheless, based on available birth rate data, we estimate being able to include 100 women in the control group and 100 women in the intervention group during the study period. We estimate that the study will have the power to detect a clinically relevant increase in women’s overall satisfaction with antenatal care from an expected 65% among Somali women receiving individual care to 82% in those receiving gANC (approximating rates for Swedish speaking women in a national population based study^50^ with 80% power and an alpha of 20%, with 70 women in each group). To have similar power to detect differences in mean scores on the Edinburgh Postnatal Depression Scale (a hypothesised reduction from a mean of 8.0 in the control group— similar to that found in studies of migrant women, to 6.0 in the gANC group—similar to that found in Swedish population-based studies,^51^ 63 women are required in each group. Allowing for 20% loss to follow-up at the time of data collection with women 2 months postpartum, 174 women will need to be recruited.

Differences between groups will be described as ORs and 95% CIs after estimation by means of logistic regression analyses. Comparison of means will be undertaken using t-tests where data are normally distributed or medians compared using Mann-Whitney U tests if not.

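### Women in group antenatal care share a group, midwives and interpreter, but the named tests and the sample size treat all women as independent; the confidence intervals will be somewhat too narrow and no ICC is planned for the future trial

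*Protocol article*

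**What the plan says.** The section on the intervention states: "Each group will consist of six to eight women and partners (or another support person) for optimal group dynamics and dialogue". Each group has its own assigned midwives and interpreter help. The section on language and integration adds that two interpreters alternate at site 1. The Introduction describes standard care as individual appointments with one midwife, and this is what the controls received.

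Under the sample size heading, the article plans for a rise in satisfaction "from an expected 65% among Somali women receiving individual care to 82% in those receiving gANC", "with 80% power and an alpha of 20%, with 70 women in each group". For the Edinburgh Postnatal Depression Scale (EPDS) it assumes "a hypothesised reduction from a mean of 8.0 in the control group" falling "to 6.0 in the gANC group", for which "63 women are required in each group". It then allows for 20% loss and arrives at 174 women to recruit.

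The analysis follows in the same section: "Differences between groups will be described as ORs and 95% CIs after estimation by means of logistic regression analyses". Scores are compared by t-test or, if not normal, by Mann-Whitney U test. Group, midwife and interpreter appear nowhere in that section.

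The Design section lists among the study's purposes "the calculation of appropriate sample sizes for future controlled trials", and the sample size section repeats this aim for possible randomised trials.

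**The concern.** Group membership exists in the intervention arm only. The logic model (Table 1) expects the benefit to come from dialogue within the group, mutual understanding and social contact. If that mechanism works, women in the same group will tend to resemble one another on satisfaction and emotional well-being, which are the two primary outcomes. T-tests and Mann-Whitney tests assume independent observations, as does logistic regression unless a cluster term or robust variance is added.

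Two things are at stake. First, the intervals and tests for both primary outcomes would look more precise than they are. Second, a later trial of group care needs a within-group ICC for its sample size, and this study, which is meant to supply planning figures, does not list one among its outputs.

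**Working it through.** **1. Does the stated sample size hide an allowance for clustering?**
Inputs from the sample size section: 65% against 82%, power 80%, alpha 20% (sidedness not stated), 70 per arm.
- The two-proportion formula for independent data, two-sided alpha 0.20, gives 60 per arm, or 72 with continuity correction. The stated 70 is close to the latter.
- 2 × 70 / (1 − 0.20) = 175, against 174 stated.

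So the satisfaction figure is an independent-data calculation. The EPDS figure cannot be checked as firmly because no standard deviation is given: 63 per arm implies an SD of 5.29 at two-sided alpha 0.20, or 4.01 at 0.05. The text mentions no design effect for it.

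**2. Cluster size in the analysis.**
The midpoint of six to eight is 7. With the planned 20% loss, 7 × 0.8 = 5.6 analysed women per group. It is lower at site 2, where groups are mixed and only Somali-born women are study participants. Results for 7 are shown as an upper case.

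**3. Design effect in the group-care arm.**
DE = 1 + (m − 1) × ICC. The ICC is an assumption, 0.01 to 0.10.

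**4. Effect on the log odds ratio.**
Per-woman variance terms: control 1/(0.65 × 0.35) = 4.396; group care 1/(0.82 × 0.18) = 6.775. The group-care arm contributes 6.775/11.171 = 0.607 of the variance, so

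SE ratio (true/naive) = √(1 + 0.607 × (DE − 1)).

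Error of a nominal 5% test = 2 × (1 − Φ(1.96 / SE ratio)).

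| Women per group | ICC | DE | SE ratio | Error | 95% CI coverage |
|---|---|---|---|---|---|
| 5.6 | 0.01 | 1.05 | 1.014 | 5.3% | 94.7% |
| 5.6 | 0.05 | 1.23 | 1.067 | 6.6% | 93.4% |
| 5.6 | 0.10 | 1.46 | 1.131 | 8.3% | 91.7% |
| 7 | 0.01 | 1.06 | 1.018 | 5.4% | 94.6% |
| 7 | 0.05 | 1.30 | 1.087 | 7.1% | 92.9% |
| 7 | 0.10 | 1.60 | 1.168 | 9.3% | 90.7% |

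These use the planning rates. If the arms contribute equally (equal rates, or EPDS with equal SDs), the ratio is √((1 + DE)/2). At 5.6 women per group it is 1.011, 1.056 and 1.109, with errors of 5.3%, 6.3% and 7.7%.

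**5. Effect on sample size and power, at 5.6 per group.**
- Satisfaction, difference in proportions: the group-care share of the variance is 0.1476/(0.2275 + 0.1476) = 0.393, so n = 70 × (1 + 0.393 × (DE − 1)) = 72, 77 and 83 per arm for ICC 0.01, 0.05 and 0.10.
- EPDS: n = 63 × (1 + DE)/2 = 65, 71 and 78 per arm.
- If power is exactly 80% at 70 and 63 per arm under independence, it falls at ICC 0.10 to about 75% for satisfaction and 74% for the EPDS.
- The article expects about 100 women per arm, so 100 × 0.8 = 80 completers. That covers both outcomes at ICC 0.05 and the EPDS at 0.10. For satisfaction at ICC 0.10 it falls short of 83 when scaled from the stated 70. Without continuity correction, 80 completers still give about 84% power at alpha 20%.

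**6. How well could the ICC be estimated?**
100/8 to 100/6 gives about 13 to 17 groups, and more if site 2 groups hold few study women. With 15 groups of 5.6 and a true ICC of 0.05, SE ≈ √[2(1 − ICC)²(1 + (m − 1)ICC)² / (m(m − 1)(k − 1))] = √[2 × 0.95² × 1.23² / (5.6 × 4.6 × 14)] ≈ 0.09. The estimate would be imprecise.

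**The case against.** The best defence has four parts.

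- **Feasibility aim and condensed text.** The article gives two sentences of analysis for a feasibility study with historical controls, and logistic regression does not by itself exclude robust standard errors or a random effect. This has some force for the regression. It has little for the t-tests and Mann-Whitney tests, which are named and assume independence, or for the sample sizes, which are stated. The article also makes a power claim and promises 95% intervals, so the feasibility label does not remove the point.
- **Unknown and possibly small effect.** The ICC is assumed, and at 0.01 to 0.02 the effect is trivial. Loss to follow-up and the mixed groups at site 2 reduce the effective cluster size. This stands, and the figures above reflect it.
- **Midwives shared in both arms.** Site 1 has ten midwives and site 2 has three, so treating each control woman as her own cluster is a simplification. This stands and should be acknowledged in the analysis.
- **Group identity may already be recorded.** Women are allocated to groups and midwives complete a checklist after each session. Nothing says the identifier is absent, so the request is to link it to the outcome data.

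A reader might also infer that the figures handed to a future trial are wrong. The documents do not support that. Recruitment and retention rates, satisfaction proportions, and EPDS means and standard deviations are essentially unaffected by within-group correlation. What is missing is the ICC.

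**Conclusion.** The point holds in a moderate form. The named tests and the stated sample sizes ignore a grouping that exists in one arm only. For any positive within-group ICC the 95% intervals for both primary outcomes are therefore too narrow and the stated power is somewhat optimistic. On an assumed ICC of 0.01 to 0.10 and 5.6 analysed women per group, the true standard error of the log odds ratio is about 1% to 13% larger than the naive one (2% to 17% with 7 per group), and the error of a nominal 5% test is about 5.3% to 8.3%.

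The direction follows from the design; the size rests on the assumed ICC and cluster size. Nothing here shows that a conclusion would reverse. The lasting loss is to planning: a future sample size taken from this study without an ICC would be too small if within-group correlation is present. This should be fixed, but it does not invalidate the study.

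**What to change.** 1. Link each group-care participant to her group in the outcome dataset.
2. Analyse both primary outcomes with a partially nested model (random intercept for group in the group-care arm only), or with cluster-robust standard errors and a small-sample correction suited to roughly 13 to 17 groups.
3. State that midwives are shared in both arms and that the model does not fully capture this, or add a sensitivity analysis by midwife.
4. Report the within-group ICC for each primary outcome with its confidence interval, labelled as an imprecise input for a future trial.
5. Restate power for both outcomes over an assumed ICC range, using the expected number of analysed study women per group.

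The cost is one linked variable, a change of analysis wording and slightly wider intervals. These changes require no extra recruitment and no change to care.

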#### Initial dialogue and choosing study settings

In the municipality chosen for site 1, the number of Somali immigrants had increased fivefold during the last decade and the ANC midwives had begun to rethink how they were providing care. At the same time, there was awareness of lower ANC attendance and adverse outcomes among childbearing Somali-born women in Sweden,^8^ and a need for more appropriate explanations of ANC routines had been highlighted in interviews with Somali-born women.^33^ This prompted a dialogue between the principal investigator and the ANC midwives, outlining the possibility of evaluating an alternative model of care. The ANC clinic is located in a primary healthcare centre staffed by 10 midwives, within a public hospital located outside the city centre. It caters for approximately 75% of all pregnant women in the municipality and almost all of the pregnant immigrant women in the municipality, which in total has 50 000 residents. The majority of the Somali-born women visiting the clinic live in two areas situated approximately five kilometres away, necessitating use of a car or public transport.

At site 2, the ANC clinic is located in a family health centre in a suburb of the capital city. Close collaboration takes place between ANC midwives, social workers, child health nurses and the open playgroup located in the same building. Three ANC midwives are employed, and the target area includes two residential areas with different sociodemographics; with primarily Swedish-born residents in one area and non-Swedish born residents and second-generation immigrants in the other. Somali-born residents have lived in this area for more than 25 years, and midwives reported that most Somali-born pregnant women and families were able to communicate in Swedish. Integration of families of different cultural backgrounds is actively encouraged at the clinic. Initial discussions revealed that the midwives believed group antenatal care for women of mixed cultural backgrounds (with interpreters available if needed) would contribute positively to integration. As a result, it was agreed that integrated groups would be more appropriate and acceptable at this site.

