#### Addressing language and integration

To respond to the diverse needs identified at the two ANC clinics and to assess advantages and disadvantages with both homogeneous and heterogeneous groups regarding language and cultural background, it was decided that gANC would be offered to Somali-born women at site 1. A large number of Somali migrants had settled in this municipality in recent years, and this meant that many were not yet fluent in Swedish. At site 2, gANC would be offered to all women attending the clinic, in integrated groups. At site 1, the need for a Somali interpreter at each session was anticipated. Since a finding in the FGDs was that continuity of known Somali interpreters had been a previous success factor, it was decided to engage two experienced interpreters who could alternate. At site 2, it was anticipated that the need for interpreters in different languages would vary and thus they would be engaged when needed.

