### Phase III: design and methods for the historically controlled evaluation of the intervention

#### Participants and recruitment

At both sites, primiparous and multiparous Somali-born women are recruited to the study. Recruitment and retention of participants to clinical studies is a well-documented challenge in research across languages and cultures.^49^ We therefore thoroughly planned how to optimise the recruitment and information processes in relation to eligible women and adjusted processes to local prerequisites at both sites. The Somali-speaking research assistant is based at site 1 where most needed and where the majority of the recruitment is performed. In site 2, team member MA is involved with recruitment, information and data collection, supported by the Somali-speaking research assistant form site 1. All pregnant Somali-born women attending the two ANC clinics receive brief information about the study from the midwives during their first visit, and if they agree to receive further information, they are then contacted by the research assistant or MA after the first ANC visit, either by telephone or face to face for further oral and written information in Somali, English or Swedish, as needed.

Inclusion criteria are being born in Somalia and <25 weeks of gestation. Exclusion criterion is a health condition preventing participation in group antenatal care, that is, severe mental health condition or if the pregnancy care were to be transferred to a specialist obstetric clinic. During the first 18 months of the study, recruited women were included in the control group receiving standard individual care, and in the following 18 months, women are included in the intervention group. All women are informed verbally and orally about the purpose of the study and that participation is voluntary. Women included in the control group were informed that their perspectives about their care would contribute knowledge valuable for a proposed intervention study aimed at improving antenatal care for migrant women.

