#### Data collection for the intervention

##### Questionnaires

Questionnaire data are collected at three time points (Q1, Q2, Q3). The baseline measurement (Q1) is conducted after recruitment, that is, before gestational week 25. Women are contacted for a face-to-face or telephone structured interview in Somali, Swedish or English at a place of their choice. Q1 includes questions on background (parity, education, income, occupation), migration (time of residence, reason for migration, migration status, language) and social support, psychological and physical well-being, knowledge of danger signs and the health system and expectations about the upcoming birth. Data for Q2 are collected in late pregnancy, after gestational week 35, in the same manner. Q2 includes questions on experiences of care and information during the ongoing pregnancy, knowledge of the health system, pregnancy and birth, social support and psychological and physical well-being and expectations for the upcoming birth. Q3 is administered 2 months postpartum and includes questions regarding the overall experience of pregnancy, ANC, birth and psychological and physical well-being. After each interview, a small gift is offered as a token of appreciation for women’s participation.

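### Non-randomised before-and-after comparison: the tests named for means, including EPDS, cannot adjust for case mix or site, and no adjustment is stated for the satisfaction odds ratio

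*Protocol article*

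**What the plan says.** **Allocation.** The study arm is set by recruitment period. Under Design: "Women in the control group were recruited between October 2016 and April 2018 and recruitment of women into the intervention began in May 2018". Participants and recruitment says the same: "During the first 18 months of the study, recruited women were included in the control group receiving standard individual care".

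**Sites.** The section on choosing study settings reports that at site 1 "the number of Somali immigrants had increased fivefold during the last decade". Addressing language and integration adds: "A large number of Somali migrants had settled in this municipality in recent years, and this meant that many were not yet fluent in Swedish". By contrast, the Somali-born community at site 2 has been established for more than 25 years, and "midwives reported that most Somali-born pregnant women and families were able to communicate in Swedish". Most recruitment takes place at site 1. No split by site and period is given.

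**Baseline data.** According to the Questionnaires section under data collection, "Q1 includes questions on background (parity, education, income, occupation), migration (time of residence, reason for migration, migration status, language". Q1 also covers psychological well-being, but the article does not say whether the EPDS itself is given at Q1.

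**Analysis.** Two sentences at the end of Sample size issues give the group comparison. For binary outcomes: "Differences between groups will be described as ORs and 95% CIs after estimation by means of logistic regression analyses". For means: "Comparison of means will be undertaken using t-tests where data are normally distributed or medians compared using Mann-Whitney U tests if not". The primary outcomes are the overall rating of antenatal care and the EPDS, and the EPDS is powered on mean scores (8.0 against 6.0).

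**Intended conclusion.** The main purpose is feasibility and planning of later randomised trials. The Discussion nevertheless expects the study to show whether gANC improves women's experience of care.

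**The concern.** Nothing in the design balances the two groups, so the analysis has to deal with differences in who was recruited when. The protocol's own introduction links language difficulty and unfamiliarity with the care system to poorer care. Time in Sweden and fluency are therefore plausible predictors of both satisfaction and emotional well-being, and the two sites differ sharply on them.

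The sentence on means is the firmer ground for the point. A t-test or Mann-Whitney test is a positive choice of method, and neither can take site, parity, education, time in Sweden or a baseline score. For satisfaction, logistic regression could carry these variables, but the text does not say that it will. Confounding is not mentioned in the article. The limitation discussed is generalisability.

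Two things are at stake: the reading of the impact result, and the effect size that would be carried forward into sample-size planning for a randomised trial.

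**Working it through.** **1. The plan's own figures.** Pooled-variance formula for two proportions, 65% against 82%, 80% power, alpha 20% two-sided: 60 per group without continuity correction and 72 with it, the latter within 2 of the stated 70. Loss to follow-up: 140 / (1 - 0.20) = 175, against the stated 174. The planned difference is 17 points, an odds ratio of (0.82/0.18) / (0.65/0.35) = 2.45. This point disputes none of these figures.

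**2. What each named method can use.**

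| Outcome | Method named | Can it carry site and Q1 variables? | Does the article say it will? |
|---|---|---|---|
| Satisfaction (binary) | Logistic regression | Yes | Not stated |
| EPDS (mean or median) | t-test or Mann-Whitney | No | Not possible |

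**3. Conditions for bias.** A variable biases the crude comparison only if it predicts the outcome and also differs between periods. The article gives reasons to expect the first condition. It gives no data on the second. The fivefold growth at site 1 came before the study, and the site difference matters only if site share changes between periods.

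**4. Illustrative size for satisfaction (assumed inputs; none are in the article).** With no gANC effect:

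spurious difference = (satisfaction gap between types of women) x (change in their share)

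- 0.20 x 0.15 = 3 points; 3/17 = 18% of the planned difference; 65% to 68% is OR 1.14
- 0.20 x 0.20 = 4 points; 4/17 = 24%; 65% to 69% is OR 1.20
- 0.30 x 0.20 = 6 points; 6/17 = 35%; 65% to 71% is OR 1.32

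The sign follows the direction of the shift. If the less settled share rose instead, the same products would count against gANC.

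**5. Effect on error rates.** Control rate 65%, 70 per group, normal approximation on the risk difference as a stand-in for the OR interval. P(interval wrongly excludes no effect, in the direction of the bias) = Phi(d/SE - z), with SE = sqrt{[p(1-p) + q(1-q)]/70}.

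- d = 0.06: SE = sqrt[(0.2275 + 0.2059)/70] = 0.0787; Phi(0.762 - 1.960) = 0.116, against 0.025 with no bias
- d = 0.04: SE = sqrt[(0.2275 + 0.2139)/70] = 0.0794; Phi(0.504 - 1.960) = 0.073
- At the stated alpha of 20%, read as two-sided (z = 1.282): 0.30 and 0.22, against 0.10
- Bias against gANC, d = -0.06: SE = 0.0819; Phi(0.733 - 1.960) = 0.110

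**6. EPDS.** The same product applies. If two types of women differed in mean EPDS by as much as the planned effect (2.0 points) and their share moved by 20 points, the spurious difference would be 2.0 x 0.20 = 0.4 points, or 20% of the target. This too is an assumption.

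**The case against.** The strongest reply has four parts.

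- **The logistic sentence is silent, not unadjusted.** A reader might infer that it commits the study to a crude odds ratio. It does not. Logistic regression can include covariates, the relevant variables are collected, and a journal article commonly leaves the covariate list to a full protocol or analysis plan. This part stands: for satisfaction, the most that can be said is that no adjustment is stated.
- **No drift during the study is described.** A reader might infer from the growth at site 1 that the population was changing between the two cohorts. The growth is over the decade before the study. The periods are adjacent, the clinics and eligibility criteria are the same, and all eligible attenders are approached. This also stands: a shift is plausible but not documented.
- **The direction is open.** It is tempting to conclude that case mix would favour gANC. The only trend the article gives is a growing, recently arrived community at site 1. If that continued, the bias could run the other way. This stands.
- **The study is mainly about feasibility and is openly described as historically controlled.** This lowers the priority but does not remove the point, because an effect is powered for and an impact conclusion is expected.

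None of this answers the sentence on means, which names methods that cannot adjust for a primary outcome.

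**Conclusion.** The point holds in a limited form. For the EPDS, the article fixes tests that cannot account for measured differences between two consecutive cohorts. For satisfaction, it leaves open whether any adjustment will be made. Differences in time in Sweden, language, parity or site share between periods could therefore be read as a gANC effect, or could hide one.

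The size cannot be determined from the article. The 3 to 6 points on satisfaction (18% to 35% of the planned 17), and the rise in one-sided error from 2.5% to as much as about 12%, rest wholly on assumed gaps and shifts. They show what moderate imbalance could do, not what is expected. The article does not support saying that case-mix change will be reported as a gANC effect.

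Given the feasibility purpose, this is a recommended improvement and not a condition for the study to proceed.

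**What to change.** In the analysis paragraph of Sample size issues:

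- State that the primary comparisons are regression models: logistic for satisfaction and linear for EPDS, with robust or bootstrap intervals if EPDS is skewed.
- Include group, site, parity, education, and either time in Sweden or language from Q1. Add the Q1 EPDS score to the EPDS model if the scale was given at Q1.
- Keep the set this short. At the planned rates, about 70 x 0.35 + 70 x 0.18 = 37 of 140 women would be in the not-satisfied category.
- Fix the set before gANC outcomes are analysed.
- Show crude results and Q1 characteristics by period and site next to the adjusted results.
- Say that unmeasured differences and change over calendar time remain a limitation that adjustment cannot remove.

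The cost is wording and a few degrees of freedom. The Q1 items are already collected and site is known for every woman.
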